## Methods

### Ethics

The study procedures below reflect the protocol version 1.3 as approved by the National Research Ethics Service (now part of the Health Research Authority). The approval was from Yorkshire & The Humber Leeds East Research Ethics Committee on 13 September 2016 (REC reference 16/YH/0371). Local approvals from the Leeds Teaching Hospitals NHS Trust and The Christie Research and Innovation Department were also obtained. Protocol amendments will be communicated via written statements and verbally reiterated where appropriate to the funder, trial teams, clinicians, steering and project management groups and trial registries.

### Patient sample

The sample will include two groups of participants at both The Christie Hospital Manchester (C) and Leeds Teaching Hospitals NHS Trust (L):Patients receiving radical RT for prostate cancer (including radiotherapy for prostate cancer +/− hormonotherapy+/− brachytherapy boost) (C & L).Patients receiving pelvic chemoradiotherapy including cervical (C & L), anal (C & L), rectal (L), vaginal (L), vulval (C) and endometrial (C).

### Inclusion criteria

Patients will be eligible ifThey have a diagnosis of (1) prostate cancer requiring radical radiotherapy treatment (including radiotherapy +/− brachytherapy boost) or (2) anal, rectal, cervical, endometrial, vaginal or vulval cancer requiring chemoradiotherapy.Aged 18 years or over.Attending St James’ University Hospital or The Christie Hospital Manchester.Able and willing to give informed consent.Read and understand English have access to the internet at home.

### Exclusion criteria

Patients were excluded if taking part in other clinical trials involving the completion of extensive PRO or QOL measures or exhibiting overt psychopathology/cognitive dysfunction.

### Patient pathways

The chemoradiotherapy pathways (cervical, anal, rectal, endometrial, vaginal and vulval patients) are very similar at both centres. However, the cervical patients in Leeds get a brachytherapy (BT) boost at 5 weeks and The Christie patients undergo this at 6 weeks. At Leeds after completion of radiotherapy, rectal patients (post-surgery) are followed up by the surgeons. Patients will be encouraged to complete AE reporting for radiotherapy toxicity but will be informed the surgical team will not be looking at the patient-reported data at 12 and 24 weeks. However, outcome measures will still be collected at 24 weeks. The radical prostate treatment pathway is similar at both centres (The Christie and Leeds); however, The Christie offers a 6-week follow-up via the telephone. All treatment pathways were mapped, and a detailed flow charts were made including timelines, toxicities, treatment visits and health personnel involved [59].

### Comparability between centres

Although the Leeds and The Christie treatment schedules differ slightly for each of the cancer sites, the treatment volumes will be comparable. Similarly, the timescales of toxicity will also be comparable, e.g. acute bowel effects from pelvic RT usually start from 8th to 9th fraction, i.e. at end of the second week.

### Design

This study is conducted at two centres (The Christie (C) and Leeds (L) employing a prospective randomised two-arm parallel group design with repeated measures and mixed methods. Participants will be randomised to either the intervention arm (eRAPID RT plus usual care) or the control arm (usual care) with 1:1 allocation). See Fig. 3 for the Trial Flow diagram.

**Fig. 3 Fig3:**
[figure not shown]
Trial flow diagram for the eRAPID radiotherapy feasibility pilot study

### eRAPID intervention

Only patients randomised to the intervention will complete the eRAPID online symptom/AE report within 24 h of study entry (forming the baseline symptom report) and then weekly (or when experiencing symptoms) for 12 weeks (6 weeks during treatment and 6 weeks post-treatment) and at 18 and 24 weeks. Patients in the eRAPID intervention arm will also complete self-efficacy and patient activation measures and a questionnaire to assess their ability to use the online system (system usability scale).

All patients (either eRAPID or usual care) complete baseline measures (pre-randomisation) on paper and at 6, 12 and 24 weeks.

The timings of online completion and the outcome measures were chosen based on the RT schedules and the follow-up pathways, aiming to find a schedule of completions that fits but allows for the slight differences between the two centres.

### Usual cancer care

Patients are provided with verbal and written information on treatment benefits and expected AEs, and instructions on how to manage AE and contact the hospital including out-of-hours. They have a nurse/clinical oncologist/radiographer assessment before starting treatment and are given information on how to manage AE and out-of-hours contact numbers.

### Recruitment

Patients will be recruited from RT departments, outpatient clinics and day-case wards at Leeds Teaching Hospital NHS Trust and at The Christie Hospital Manchester (CHM). Eligible patients will be identified by screening of clinic, in-patient or day-case lists by the clinical or administration staff. Consultants responsible for the care of patients are informed via letter or email.

After introduction from clinical staff, a researcher (who has received Good Clinical Practice training (GCP) will explain the study, provide an information sheet (Additional file 1: Appendix 2) and obtain consent (Additional file 1: Appendix 3) at this or the patient’s next visit. Participants are free to withdraw from the trial at any time without giving reasons and without prejudicing any further treatment. Reassurance is given that anonymity will be maintained (patients are issued a study number), and data collected will be treated in the strictest confidence and held in accordance with the Data Protection Act 1998.

### Randomisation

Participants are randomised with 1:1 allocation to intervention and control groups, performed centrally at the University of Leeds Clinical Trials Research Unit (CTRU) using the 24-h telephone system. Patients randomised to the intervention arm receive training in using the eRAPID system.

Patients are already stratified by cancer centre (Leeds or Manchester) and will be further stratified by cancer site, e.g. prostate or cancer requiring chemo RT (cervix, anal, rectal, vaginal, endometrial and vulval). A diagrammatic representation of the stratification factors is presented in Fig. 4.

**Fig. 4 Fig4:**
[figure not shown]
Stratification factors for eligible patients by hospital and cancer site

### Training

#### Staff

Staff are trained by the researchers reinforced by a user-manual providing scenarios of an ‘example’ patient and how to interact, interpret and access the PRO data in the EPR and incorporate this data into their consultations. It is stressed that PRO data should be seen as a supplementary resource to aid management decisions. We will explore and reassure staff that using eRAPID will not extend consultation times.

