Participant withdrawal feedback form	At point of withdrawal							
End of study patient questionnaire	24 weeks							X
Clinician questionnaires								
Clinician eRAPID feedback form (eRAPID intervention arm only)	At routine hospital appointments throughout the study		X	X	X	X	X (except rectal)	X (except rectal)
Clinician record of CTCAE	To be completed by clinician at the follow-up appointment 4–6 weeks after completion of treatment (exact time-point will be different for different disease groups)							

Statistical analysis of the recruitment and attrition rates, clinical process measures and patient outcome data is the responsibility of the CTRU Trial Statistician under the supervision of the Supervising Statistician. A full statistical analysis plan has been written by the CTRU Trial Statistician. A health economic data analysis will be undertaken by a health economist from the academic Unit of Health Economics (AUHE), based on the health economics analysis plan (HEAP). Interview data will be processed by the research teams in the two participating centres. All analyses will be conducted according to the intention to treat (ITT) principle using SAS statistical software.

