### Staff interviews and questionnaires

Up to five health professionals from each disease group will be interviewed at the end of the study to determine their views of eRAPID, the perceived value and use of patient data in clinical practice, exploring if eRAPID improves the detection, documentation and management of AE and support treatment decision-making. Perceptions of staff training needs and recommendations for improving the system will also be explored.

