### Clinical process measures

The number of telephone calls to hospital staff and weekly/additional AE reports completed using the eRAPID system will be summarised. Clinician and staff acceptability will be explored during the staff interviews. Initial interviews will determine any anticipated barriers to the use of eRAPID, whereas exit interviews will explore actual issues that prevented staff from incorporating information into routine practice. Clinicians will be asked when and how they made use of the additional information, and how this benefitted them.

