## Discussion

This paper describes the protocol for the eRAPID feasibility study in patients undergoing pelvic radiotherapy. eRAPID is a complex web-based intervention designed to improve the systematic reporting of AE during cancer treatment and improve patient care and experiences. We aim to determine the acceptability and feasibility from both the perspective of patients undergoing pelvic radiotherapy+/− chemo-radiotherapy and their health professionals to determine effect sizes and select an appropriate outcome measure for a future RCT. We also aim to refine the intervention by exploring patient and staff views.

The immediate severity-related guidance generated from eRAPID on how to manage AE is a unique feature of our system compared to other ePRO web-portals [35, 38]. We hypothesise that eRAPID will ultimately have benefits for patients and staff. For patients, it may enable earlier symptom detection and improved self-management, lead to more timely admissions to manage more serious AE, improve supportive medication use and appropriate health service contacts. For staff, it may reduce the number of contacts, save time spent on enquiring about and recording AEs, focus attention and support decision-making during consultations.

The ultimate success of eRAPID will depend on how patients and staff engage with and appreciate the potential benefits of the system. This pilot study will determine the acceptability and feasibility of the complex intervention for patients and staff and determine any changes required to improve the system prior to evaluation in an RCT. The study is funded as part of 5-year programme and has the potential to provide a cost-effective solution for follow-up for pelvic radiotherapy patients by reducing hospital or primary care contacts. In addition, it will help to create a comprehensive database of RT AE and deliver vital PRO information on treatments.

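### Staff training gives an untested assurance about consultation length, and one clinician question presumes benefit: a limited, cheaply removed risk of expectation bias in the staff-views component

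*Protocol article*

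**What the plan says.** Under Training, Staff, the article says "Staff are trained by the researchers reinforced by a user-manual", and adds: "We will explore and reassure staff that using eRAPID will not extend consultation times".

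Under Statistical analysis, Clinical process measures, it says "Clinician and staff acceptability will be explored during the staff interviews". It continues: "Initial interviews will determine any anticipated barriers to the use of eRAPID". Exit interviews are to look at problems that stopped staff using the reports in practice. The paragraph closes: "Clinicians will be asked when and how they made use of the additional information, and how this benefitted them".

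Staff interviews and questionnaires sets the purpose as to "determine their views of eRAPID, the perceived value and use of patient data in clinical practice". It asks whether eRAPID improves detection, documentation and management of adverse events, and invites suggestions for improvement.

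The Discussion lists among possible staff benefits that eRAPID may "save time spent on enquiring about and recording AEs".

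On who handles the interviews, the article says "Interview data will be processed by the research teams in the two participating centres". The Qualitative data section plans independent analysis by two researchers and an active search for negative cases.

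**The concern.** Consultation length is a burden that the team evidently expected staff to raise, or no reassurance would be needed. Training answers the question before the study has looked at it. The people who receive that answer then become the respondents for the staff part of the sixth aim, refining the intervention through patient and staff views. If they later report no time burden, the study cannot easily tell whether they are describing experience or repeating what they were told.

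The benefit question adds to this. Asking how something benefitted a respondent takes the benefit as given, and the article's own section on staff interviews does not word the matter that way.

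At stake is how well the staff views inform changes to the system before a trial. No treatment-arm comparison is at stake.

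**Working it through.** The article gives no figure for this bias, so the check sets the sections side by side.

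1. **What staff are told against what is known.** Training says consultations will not lengthen and cites no data. The Discussion places staff time savings under a *may*. The two statements are not strictly contradictory: one concerns total consultation length, the other time spent asking about and recording adverse events. The difference is in certainty. Training treats as settled something for which the article offers no evidence.

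2. **What is measured.** Table 1 and the Clinical process measures list under data collection count contacts, admissions, phone calls, medication and dose changes, and alerts. The section on integrity of the protocol and forms times only the completion of paper and QTool forms. Consultation duration is listed nowhere, in either arm.

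3. **What could record perceived time.** Table 2 lists a clinician eRAPID feedback form, intervention arm only, at routine appointments marked at 3, 6, 9, 12, 18 and 24 weeks (the last two not for rectal patients). Its items are not shown, so whether it already asks about time is unknown. A ceiling on the number of forms follows from the sample size section:
   - intervention patients: 168 / 2 = 84
   - forms with no attrition: 84 × 6 = 504
   - forms if the planned 30% attrition applied from the outset: 84 × 0.70 × 6 = 352.8, about 350

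   The rectal exception lowers both figures. They bound the opportunity to collect a rating; they do not measure any bias.

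4. **Which experiences the staff questions reach.**

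| Clinician's experience | Question that reaches it directly |
|---|---|
| Expected obstacles before use | Initial interviews on anticipated barriers |
| Did not or could not use the reports | Exit interviews on what prevented use |
| Used the reports and found them helpful | Question on how they were used and what benefit followed |
| Used the reports and noticed no difference | Only the neutral question on whether care improved |
| Used the reports and found consultations longer | None directly; may surface under views or suggested improvements |

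   The last two rows are the gap. The barrier questions are framed around non-use, and the benefit question around success.

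5. **Whether later steps repair it.** Two analysts and a search for negative cases protect the reading of the transcripts. They cannot undo an expectation set in training or recover an answer that was not sought. Researchers deliver the training and the centres' research teams process the interviews. The article does not say whether these are the same individuals, but some closeness between trainer and analyst is likely.

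**The case against.** The strongest reply is that the plan is more balanced than two phrases suggest. The training sentence says the matter will be explored as well as reassured. The lines just before the benefit question plan to ask about barriers before use and problems after it. The staff interview section asks neutrally whether eRAPID improves care and invites suggestions. The analysis looks for negative cases. The article summarises topics rather than printing an interview guide, and a condensed article may fairly leave the guide and the form items to the full protocol. None of the six specific aims names consultation time, and no decision to proceed to a trial is tied to it.

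Most of this stands, and it rules out stronger readings that a reader might infer:
- *Staff acceptability is steered to a favourable result.* The documents do not support this, because adverse experience is sought in several places.
- *Hindrance is never asked about.* This is wrong, given the barrier and exit questions.
- *The assurance cannot be checked at all, or the feedback form has no time item.* This goes too far. Only measured duration is clearly unlisted; perceived time could come up in interviews or on a form whose items are not shown.

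What the reply does not remove is the stated text. The word *explore* does not neutralise a sentence that also gives staff the answer. The benefit wording remains presumptive, and the barrier questions do not directly reach users who found eRAPID neutral or time-consuming.

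**Conclusion.** The point holds in a narrow form and at low severity. Staff receive an untested assurance on consultation length, no listed measure records that length, and one clinician question presumes benefit where another section is neutral. The existing safeguards reduce the resulting expectation bias but do not close the gap.

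The exposure covers trained staff and the staff interviews, which number up to five professionals per disease group. The size of any bias cannot be estimated from the article. The conclusion assumes that the training and the interviews follow the wording shown; a neutral interview guide or an existing time item on the feedback form would shrink the point further.

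Recruitment, attrition, adherence, the confidence intervals for differences between arms and the sample size are untouched.

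**What to change.** - **Training, Staff:** replace the assurance with a neutral statement that the effect of eRAPID on consultation time is not known and will be explored.
- **Statistical analysis, Clinical process measures:** ask clinicians whether and how the information helped, made no difference or hindered, including its effect on consultation length. This brings the wording into line with the neutral question under Staff interviews and questionnaires.
- **Clinician eRAPID feedback form:** confirm that it has an item on perceived consultation time (for example shorter, about the same, longer), or add one. Report it descriptively, labelled as perceived and from the intervention arm only. It comes from the same trained staff and has no control-arm counterpart, so it cannot estimate an effect on consultation length.

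The cost is two wording edits and at most one item on a form already in use, with no extra visits or patients. The one downside is that staff may be slightly less reassured at the start.

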#### Patient

Researchers demonstrate how to use eRAPID system and provide a unique user name and password to access the system, on an eRAPID ‘postcard’. Participants are given step-by-step user guide and if encounter problems (e.g. lost user names/password or problems logging on) are advised to contact the research team. Prompts to complete the eRAPID questionnaire can be sent via email or text message.

### Sample size and recruitment rate

Thirty patients per arm for each treatment type will provide valuable information on outcomes [60] (Tables 1 and 2) Allowing for 30% overall attrition, we aim to recruit a minimum of 42 patients per-arm (*n* = 84 for each treatment type) at a rate of around 15 patients per month for approximately 15 months giving an overall total of 168 patients, with a 24-week follow-up.

**Table 1 Tab1:** eRAPID RT study questionnaires and Case Report Forms (CRFs): researcher completed

Questionnaire/CRF	Time point for completion
Eligibility checklist	Baseline
Comorbidity form	End of study
Consent form	Baseline
Registration/randomisation form	Baseline
Baseline: clinical data form	End of study
Clinical process measures Number of hospital contacts Number of alerts and hospital admissions Readmissions (with reasons) Clinician records of CTCAE and RTOG Changes to supportive medications and RT and/or chemotherapy dose changes Contacts with GP/community services Safety monitoring acute admissions, cumulative deaths	Collected during a course of RT treatment and if appropriate chemotherapy cycle (from hospital records and via brief patient survey at routine clinic appointments for interim assessment of clinical contacts)
IT system functioning Telephone log of phone calls from patients Record of unscheduled server down time	Throughout the duration of the study
Death and withdrawal form	At point of death/withdrawal

**Table 2 Tab2:** eRAPID RT study questionnaires and Case Report Forms (CRFs): participant completed

Questionnaire/CRF	Description of time points for completion	Baseline	3 weeks	6 weeks	9 weeks	12 weeks	18 weeks	24 weeks
Consent form	Baseline	X						
Baseline: patient sociodemographic data form	Baseline	X						
Baseline: computer usage questionnaire	Baseline	X						
Patient-reported eRAPID symptom questionnaire (eRAPID intervention arm only)	Within 24 h of study entry and weekly during treatment and 6 weeks afterwards (12 weeks total). Then at 18 and 24 weeks.	X weekly	X weekly	X weekly	X weekly	X weekly	X (except rectal)	X (except rectal)
Patient Outcome Measures FACT-G EORTC-QLQ-C30 EQ-5D-5 L	Baseline, 6, 12 and 24 weeks	X		X		X		X
Self-efficacy, Lorig 6-item	Baseline and 12 weeks	X				X		
Patient Activation Measure (PAM)	Baseline and 12 weeks	X				X		
Use of resources form	6, 12 and 24 weeks			X		X		X
System Usability Scale	24 weeks (eRAPID intervention arm only)							X
Participant withdrawal feedback form	At point of withdrawal							
End of study patient questionnaire	24 weeks							X
Clinician questionnaires								
Clinician eRAPID feedback form (eRAPID intervention arm only)	At routine hospital appointments throughout the study		X	X	X	X	X (except rectal)	X (except rectal)
Clinician record of CTCAE	To be completed by clinician at the follow-up appointment 4–6 weeks after completion of treatment (exact time-point will be different for different disease groups)							

Statistical analysis of the recruitment and attrition rates, clinical process measures and patient outcome data is the responsibility of the CTRU Trial Statistician under the supervision of the Supervising Statistician. A full statistical analysis plan has been written by the CTRU Trial Statistician. A health economic data analysis will be undertaken by a health economist from the academic Unit of Health Economics (AUHE), based on the health economics analysis plan (HEAP). Interview data will be processed by the research teams in the two participating centres. All analyses will be conducted according to the intention to treat (ITT) principle using SAS statistical software.

